**Methods:**

This randomized controlled trial will be conducted in the First Affiliated Hospital of Changchun University of Chinese Medicine in China. Two hundred and sixteen FD patients will be randomly assigned to the compatible acupoints group, single acupoint group, or sham acupuncture group. This trial will include a 1-week baseline period, a 4-week treatment period, and a 4-week follow-up period. During the 4-week treatment period, patients will receive 20 sessions of acupuncture (weekly cycles of one session per day for 5 consecutive days followed by a 2-day break). The primary outcome will be a change in the Nepean Dyspepsia Life Quality Index from baseline to after the 4-week treatment period. Secondary outcome measures will include the dyspeptic symptom sum score, Overall Treatment Effect questionnaire, and 36-item Short Form survey. Adverse events also will be recorded. Ultraweak photon emission and metabolomics tests will be performed at baseline and at the end of treatment to explore the mechanisms of the differences between compatible acupoints and a single acupoint.

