#### Laboratory tests

Laboratory tests will be performed at two time points: baseline and at the end of treatment. In the morning, after the participant has fasted for at least 12 h, venous blood and urine will be collected at the First Affiliated Hospital of Changchun University of Chinese Medicine. Metabolomics tests will be conducted at The Jilin Ginseng Academy of Changchun University of Chinese Medicine.

Ultraweak photon emission (UPE) [23, 24] will be carried out with the biological ultraweak photon emission signal acquisition system (PMS09.1) at the Acupuncture and Moxibustion Research Institute of Changchun University of Chinese Medicine. These measurements will be performed at the baseline and at the end of the treatment time points. During the testing period, participants will wear black clothes and enter a darkroom. UPE will be detected at the RN12 acupoint before 12 a.m. over a 20-min period. The purpose of this test is to detect mean changes in UPE before and after acupuncture and to explore the mechanisms of acupuncture treatment on FD based on energy metabolism.

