### Sample size

Based on our clinical experience, changes in the NDLQI scores in the compatible acupoint group, single acupoint group and sham acupuncture group at the 4th week are expected to be 12, 8, and 4, respectively. The standard deviations in the three groups are expected to be 10, 13, and 13, respectively. The two-sided significance level is 0.05.
$$ n=\frac{\psi^2\left(\sum {S}_i^2/k\right)}{\sum {\left({\overline{X}}_i-\overline{X}\right)}^2/\left(k-1\right)} $$

A sample size of 60 patients in each group is estimated to have 80% power to detect significant differences among the three groups. To compensate for a 20% loss to follow-up, the sample size was increased to 72 patients.

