### Statistical analysis

The intention-to-treat analysis will be used for all allocated participants in the baseline condition. Baseline characteristics will be summarized across the treatment groups. Missing values will be imputed by the last observation carried forward (LOCF) method. Depending on whether the data are normally distributed, the continuous variables will be described as the mean (standard deviation) or the median (interquartile range). One-way analysis of variance (ANOVA) will be used for comparisons among the three groups. Categorical variables will be described using frequency (percentage) and compared using Fisher’s exact test. The statistical analyses will be performed using SAS 9.1.3. *P* < 0.05 will be considered statistically significant.

All efficacy analyses, which will include all participants who are randomized, will be performed using the intent-to-treat analysis. Primary comparisons (change in the NDLQI scores at week 4 relative to the baseline scores among the three groups) will be made with ANOVA. Pairwise comparisons will use the Student-Newman-Keuls method.

For the secondary outcomes, continuous variables, including the DSSS and SF-36 scores, metabolomics, and UPE, will be compared among the three groups at all follow-up time points using ANOVA. The Student-Newman-Keuls method will be used for pairwise comparisons. The OTE and adverse events will be summarized for each group and compared using Fisher’s exact tests.

Analysis of covariance (ANCOVA) or logistic regression analysis will be used in the sensitivity analysis. The sensitivity analysis will also be performed using a per-protocol analysis, which includes only those who complete ≥16 sessions and have no major protocol violations (e.g., taking other drugs during the trial).

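### Metabolomics is assigned ANOVA at a general P < 0.05 with no stated control across metabolites, so about 5% of unaffected metabolites would be called different by chance

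*Protocol article*

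**What the plan says.** The Statistical analysis section of the protocol article lists metabolomics with the continuous secondary variables (symptom score, SF-36, photon emission) and gives them all one rule: "metabolomics, and UPE, will be compared among the three groups at all follow-up time points using ANOVA". It then adds: "The Student-Newman-Keuls method will be used for pairwise comparisons". Earlier in the same section a single threshold is set for the analyses, P "< 0.05 will be considered statistically significant", with no exception for metabolomics. The Sample size section uses the same level: "The two-sided significance level is 0.05".

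Under Laboratory tests, the article says that "venous blood and urine will be collected", names the laboratory ("Metabolomics tests will be conducted at The Jilin Ginseng Academy of Changchun University of Chinese Medicine") and fixes the timing: "Laboratory tests will be performed at two time points: baseline and at the end of treatment". It does not say whether the assay is targeted or untargeted, or how many metabolites it will measure.

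The Methods part of the abstract says that the photon emission and metabolomics tests serve "to explore the mechanisms of the differences between compatible acupoints and a single acupoint".

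**The concern.** A threshold of P < 0.05 suits one pre-named score. A metabolomic assay normally returns many variables, and the article collects two specimen types. Because no summary score is defined to which a single ANOVA could be applied, the stated rule leads naturally to a separate ANOVA for each metabolite, each judged at 5%. The named pairwise method deals with three groups within one metabolite and leaves the number of metabolites unaddressed.

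At stake is the mechanistic part of the trial. Metabolites that pass an unadjusted threshold would be offered as clues to why two acupoints act differently from one, and an unknown share of them would be chance results. The primary comparison on the NDLQI does not depend on this analysis.

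**Working it through.** **Inputs from the protocol article**
- Test: one-way ANOVA among three groups, then Student-Newman-Keuls (Statistical analysis).
- Threshold: 0.05, one general value (Statistical analysis).
- Specimens: blood and urine (Laboratory tests).
- Occasions: baseline and end of treatment, so one post-baseline comparison per metabolite (Laboratory tests).

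**Inputs not in the article, taken as assumptions**
- Number of metabolites tested, m: shown from 10 to 2,000.
- Share of metabolites that truly differ, π: shown from 0 to 50%.
- Power per truly different metabolite: shown at 80% and 50%.

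The article gives no figure for metabolomics, so there is none to reproduce. Its only power figure concerns the NDLQI.

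**Step 1: expected chance findings when no metabolite is affected.** The formula is 0.05 × m. It does not require the metabolites to be independent.

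| m (assumed) | 0.05 × m |
|---|---|
| 10 | 0.5 |
| 100 | 5 |
| 500 | 25 |
| 1,000 | 50 |
| 2,000 | 100 |

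The counts add over the two biofluids. With 100 metabolites in each, 5 + 5 = 10 would be expected.

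**Step 2: what Student-Newman-Keuls contributes.** It orders three group means and tests their differences for one variable. It takes no account of m, so it leaves Step 1 unchanged.

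**Step 3: share of chance results among the metabolites declared different.** As a ratio of expected counts, the share is 0.05(1 − π) / [0.05(1 − π) + π × power]; m cancels.

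| π (assumed) | Power 80% | Power 50% |
|---|---|---|
| 0 | 100% | 100% |
| 5% | 0.0475 / 0.0875 = 54% | 0.0475 / 0.0725 = 66% |
| 10% | 0.045 / 0.125 = 36% | 0.045 / 0.095 = 47% |
| 20% | 0.04 / 0.20 = 20% | 0.04 / 0.14 = 29% |
| 50% | 0.025 / 0.425 = 6% | 0.025 / 0.275 = 9% |

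The share runs from about 6% to 100%, and nothing in the article narrows that range.

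**Step 4: what the remedy does.** Benjamini-Hochberg sorts the m P values and declares the smallest i of them, where i is the largest rank with P(i) ≤ (i/m) × 0.05. This holds the expected share of false declarations at or below 5%, for independent or positively dependent tests. With m = 100, a metabolite standing alone would need P ≤ 0.05/100 = 0.0005. With ten declared, the tenth would need P ≤ (10/100) × 0.05 = 0.005.

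**The case against.** The strongest reply is that this is silence in a condensed article. Metabolomics gets two sentences under Laboratory tests. The platform, feature filtering, any multivariate modelling and the handling of multiplicity are what a journal article commonly leaves to a full protocol or analysis plan, and neither is shown. The 0.05 line is also general enough that adjusted P values could be judged against it.

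Part of this stands. A reader might infer that the trial has no false-discovery control at all; the article shows only that none is stated. A reader might also take one test per metabolite as the authors' own wording. It is an inference, though the natural one, because ANOVA is univariate and no composite is defined.

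The reply does not remove the point. The article names metabolomics and assigns it a test, a pairwise method and a threshold. Anyone who follows those words gets the result in Step 1.

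Other stronger readings also fail:
- **That the mechanistic results would be mostly chance.** Step 3 shows that this depends on the share of true effects, which is unknown. With a panel of 10, only half a chance finding is expected.
- **That at least one false positive is virtually certain.** For 200 unaffected metabolites, 1 − 0.95^200 exceeds 0.9999, but this assumes both independence and that count. It is also a familywise quantity, whereas the remedy controls a rate.
- **That the timing is contradictory.** The phrase on follow-up time points governs a list of outcomes, some of which are also assessed at the end of follow-up. Read with Laboratory tests, it leaves one post-baseline occasion for metabolomics, and no result changes.
- **That exploratory intent is missing.** The abstract already describes these tests as exploring mechanisms. The Statistical analysis section simply does not carry that label over to the tests.

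**Conclusion.** The point holds in a limited form. The article sets ANOVA with Student-Newman-Keuls at P < 0.05 for metabolomics and states no control across metabolites. Applied as written, one test per metabolite, it would call about 5% of unaffected metabolites different.

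The 5% rate follows from the stated threshold. The absolute number rests on an assumed count of metabolites, and the share of chance results among those declared rests on assumed true effects and power. The conclusion also rests on reading the rule as one test per metabolite.

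This is an inexpensive improvement to an exploratory analysis. A reader might infer that it casts doubt on the trial's efficacy result, but the article's primary comparison is on the NDLQI and uses no metabolomic data.

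**What to change.** Add to the analysis plan, before the metabolomic data are analysed, that significance for metabolomics will be judged on Benjamini-Hochberg adjusted P values (for example q < 0.05) across all metabolites within each biofluid at the end of treatment, and that the results will be reported as exploratory. If such a rule already exists in a document not shown, refer to it.

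The smallest change keeps the planned ANOVA: adjust its P value for each metabolite, and apply Student-Newman-Keuls only to the metabolites that pass. The plan should then say that the 5% rate refers to the three-group finding, not to each pairwise statement. A contrast restricted to compatible versus single acupoints, a log scale or baseline adjustment may be worth considering, but none is needed to deal with multiplicity.

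The cost is a sentence or two and trivial analysis work, with no change to trial conduct. The downside is fewer nominally significant metabolites, including some real differences that unadjusted testing would have flagged.

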### Outcomes

The following outcomes will be assessed by independent outcome assessors. These assessors will be trained before participating in this trial and will be blinded to the group assignments. The outcome assessors will contact the participants on the phone up to three times if the participants do not respond to the assessment. The outcome assessments will be performed at three time points: at baseline, at the end of the acupuncture treatments, and at the end of the follow-up period (Fig. 3). Patient privacy information will be separated from the trial data, and the analysis and publication of trial data results will not involve patient privacy information.

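### The primary NDLQI analysis is an unadjusted one-way ANOVA of change with ANCOVA kept for sensitivity: valid under randomisation, but it gives up precision that baseline adjustment would supply from data already collected

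*Protocol article*

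**What the plan says.** All of this is in the protocol article.

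- Statistical analysis, general method: "One-way analysis of variance (ANOVA) will be used for comparisons among the three groups". One-way means that no covariate enters.
- Statistical analysis, primary outcome: "Primary comparisons (change in the NDLQI scores at week 4 relative to the baseline scores among the three groups) will be made with ANOVA". For the individual pairs of groups, the plan adds: "Pairwise comparisons will use the Student-Newman-Keuls method".
- Statistical analysis, last paragraph: "Analysis of covariance (ANCOVA) or logistic regression analysis will be used in the sensitivity analysis". The covariate is not named.
- Outcomes, where baseline is the first of the listed assessment times (the quote is cut before the last one is named): "The outcome assessments will be performed at three time points: at baseline, at the end of the acupuncture treatments, and at the end of the". Baseline NDLQI is therefore in hand for each assessed participant.
- Sample size, on the mean changes in the compatible, single and sham groups: "at the 4th week are expected to be 12, 8, and 4, respectively". On their spread, it gives: "The standard deviations in the three groups are expected to be 10, 13, and 13, respectively". On the test level, it gives: "The two-sided significance level is 0.05". The planned size is 60 per group, raised to 72 for losses.

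I take week 4 as the primary time point, as the Statistical analysis and Sample size sections do. The Primary outcome section words the time point differently, which is a separate matter.

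**The concern.** A change score uses the baseline, but with its slope fixed at 1. ANCOVA estimates that slope. Unless the best slope happens to be 1, the change score carries extra noise. It also leaves chance baseline imbalance in the estimate of the particular trial: with equal SDs and a correlation below 1, a group that starts lower by chance is expected to gain more through regression to the mean.

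The precision matters most for compatible versus single acupoint, which the Background gives as the aim of the trial. That is a difference of 4 points on the sponsor's own figures, and it is the contrast with little power to spare.

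A second weakness sits in the same model. ANOVA and Student-Newman-Keuls (SNK) use one pooled variance, while the Sample size section expects a smaller SD in the compatible group than in the other two.

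**Working it through.** **Inputs.** From Sample size: mean changes 12, 8, 4; SDs 10, 13, 13, read as SDs of change; 60 per group; two-sided 0.05. Assumed, because the article does not give them: the baseline to week-4 correlation ρ, and the ratio of the baseline SD to the week-4 SD.

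**The plan's own figure.** The mean variance is (100+169+169)/3 = 146, and the between-group term is (16+0+16)/2 = 16. With ψ = 2.21 for 80% power, the plan's formula gives n = 2.21² × 146/16 ≈ 45 per group. At 60 per group the overall F test has 90.6% power. So 60 does not reproduce at 80% (59 per group gives 90%). That mismatch is a separate matter; here it shows that the overall test is not short of power on the stated inputs.

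**Precision of the two analyses.** Write SD_b and SD_f for the baseline and week-4 SDs.

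- Change score: variance = SD_b² + SD_f² − 2ρ·SD_b·SD_f.
- ANCOVA: variance = SD_f²(1 − ρ²).
- Difference = SD_b² − 2ρ·SD_b·SD_f + ρ²·SD_f² = (SD_b − ρ·SD_f)², which is never negative.

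Apart from one degree of freedom, ANCOVA is never less precise. The two tie when ρ = SD_b/SD_f. If SD_b = SD_f, the variance ratio is (1 − ρ²)/[2(1 − ρ)] = (1+ρ)/2.

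**Compatible versus single, 60 per group.** The standard error of the difference is √[(100+169)/60] = 2.117, so z = 4/2.117 = 1.889 and power ≈ Φ(1.889 − 1.960) = 47%. This is a two-sample approximation at 0.05. With ANCOVA, z is divided by √ratio:

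| ρ (assumed) | variance ratio | z | power |
|---|---|---|---|
| change score | 1 | 1.89 | 47% |
| 0.3 | 0.65 | 2.34 | 65% |
| 0.5 | 0.75 | 2.18 | 59% |
| 0.7 | 0.85 | 2.05 | 54% |
| 0.9 | 0.95 | 1.94 | 49% |

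This contrast needs 132 per group for 80% power with change scores. At a ratio of 0.65 it still needs 132 × 0.65 ≈ 86, more than 60 or 72.

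The 47% is not the power of the planned test. Simulating the pooled SNK procedure with means 12, 8, 4 and SDs 10, 13, 13 gives about 43% at 60 per group.

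**Pooled variance.** The pooled standard error of any pairwise difference is √(2 × 146/60) = 2.206.

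- Single versus sham: true standard error √(338/60) = 2.373. The nominal cut-off of 1.96 becomes 1.96 × 2.206/2.373 = 1.82, a two-sided error of about 7%.
- Compatible versus single: true standard error 2.117. The cut-off becomes 1.96 × 2.206/2.117 = 2.04, an error of about 4%.

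Simulation of SNK agrees: about 7% for single versus sham when the compatible group differs, and about 4% for compatible versus single when sham differs. With the third group only 8 points away, the largest gap the plan expects, the figures are 6.8% and 4.1%. With all three means equal, every pairwise error is below 3.5%.

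**The case against.** The strongest reply is that nothing here is an error. The change-score ANOVA is prespecified, unbiased under randomisation and matched to the quantity used for the sample size. ANCOVA is already planned, and naming its covariate may be left to a fuller document. All of that stands, and it limits the point to efficiency.

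A reader might infer more, in four ways that the document does not support:

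- *That the primary analysis is biased or invalid.* Chance imbalance affects a single trial's estimate; across randomisations the estimator is unbiased.
- *That ANCOVA is strictly better for any correlation below 1, or that the baseline is thrown away.* The (1+ρ)/2 ratio needs equal SDs, and the tie at ρ = SD_b/SD_f can occur below 1. The article gives neither SD nor ρ. At ρ = 0.9 the gain is about two points of power.
- *That 47% describes the planned test.* It is a two-sample approximation; the planned pooled procedure has about 43%.
- *That adjustment rescues the compatible versus single comparison.* It does not reach 80% anywhere in the range shown. The low power of that contrast is a sample-size issue.

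It is also fair to say that the unequal-variance problem is distinct. ANCOVA with a pooled variance would not cure it, the SDs rest on clinical experience, and the excess error is about 2 points and falls on single versus sham. What remains is that the protocol fixes the less precise model as primary when the better one needs no further data.

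**Conclusion.** The point holds as a recommendation on efficiency. The plan ranks an unadjusted change-score ANOVA above an ANCOVA that is never less precise, apart from one degree of freedom. With equal SDs and ρ from 0.3 to 0.9, both assumed, the variance falls by 35% to 5%. For compatible versus single, that is worth between about 18 and 2 points of power at 60 per group.

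The variance pooling is a smaller, separate weakness that concerns error rates. If the sponsor's SDs are right, SNK is mildly anti-conservative for single versus sham and mildly conservative for compatible versus single.

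Neither makes the trial's primary result invalid. Both can be put right by a change of wording.

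**What to change.** Make the primary model an ANCOVA of week-4 NDLQI (or its change; the group effect is the same) on group and baseline NDLQI. Name that covariate. Use heteroscedasticity-robust standard errors or group-specific residual variances, and report the pairwise differences with 95% CIs. Because SNK relies on a pooled variance, state how multiplicity over the three pairs is controlled in the new model. Treat DSSS and SF-36 in the same way, each with its own baseline. Keep the unadjusted ANOVA of change as a sensitivity analysis.

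The cost is a protocol or SAP amendment: no new visits, measurements or patients. The Trial status section dates the first enrolment to 11 April 2019, so this alters the primary analysis of a registered trial already under way. The amendment should be dated and made before unblinding; the plan to keep statisticians masked until the analysis is complete makes that possible.

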### Intervention

Participants will be randomly allocated into one of three groups: A, the compatible acupoints group; B, the single acupoint group; or C, the sham acupuncture group (control group). Two acupuncturists, who are from Chinese Medicine Practitioners in China and have at least three years of clinical experience in acupuncture practice, will perform all acupuncture sessions. Several training workshops will be provided prior to the commencement of the study to ensure that the skills of the acupuncturist are consistent. During the 4-week treatment period, patients will receive 20 sessions of acupuncture (4 weekly cycles of one treatment per day for 5 consecutive days, followed by a 2-day break). Sterile needles (0.25 mm × 40 mm/ 0.25 × 25 mm, Hwato, Suzhou, China) will be used in the trial. All acupuncture treatments and laboratory tests will be provided for free to improve adherence to the intervention protocol. Patient and acupuncturist signatures will be required after each acupuncture session to monitor adherence. Other treatments that may affect the dyspepsia symptoms will be prohibited, such as antacids, prokinetics, non-steroidal anti-inflammatory drugs, and antidepressant drugs.

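### The per-protocol sensitivity analysis, as written, can drop patients from the week-4 NDLQI comparison for drugs taken after week 4

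*Protocol article*

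**What the plan says.** Four parts of the protocol article bear on this.

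- **Per-protocol set (Statistical analysis).** This set serves a sensitivity analysis. It asks for at least 16 of the 20 sessions and, as a second condition, "no major protocol violations (e.g., taking other drugs during the trial". The drug example has no time limit other than the trial itself.
- **Length of the trial (Abstract, Methods; repeated in Study design).** "This trial will include a 1-week baseline period, a 4-week treatment period, and a 4-week follow-up period".
- **Time of the primary comparison.** The Statistical analysis section fixes it as "change in the NDLQI scores at week 4 relative to the baseline scores among the three groups". The Abstract agrees ("change in the Nepean Dyspepsia Life Quality Index from baseline to after the 4-week treatment period"), and the Sample size section plans on changes at week 4. The Primary outcome section differs: it takes the change through the end of the 4-week follow-up.
- **Drug prohibition (Intervention).** "Other treatments that may affect the dyspepsia symptoms will be prohibited, such as antacids, prokinetics, non-steroidal anti-inflammatory drugs, and antidepressant drugs". No end date is given here either.

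The main analysis set is not in doubt: "All efficacy analyses, which will include all participants who are randomized, will be performed using the intent-to-treat analysis".

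**The concern.** A per-protocol analysis describes patients treated as planned up to the moment the outcome is measured. A drug taken later cannot change a score already on file, so excluding for it adds nothing about adherence before that score. It does make membership of the set depend on an event after the outcome, and that event may be related to the outcome.

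Take a patient who attends all 20 sessions, completes the week-4 NDLQI, is still symptomatic and takes an antacid in week 6. As written, that patient leaves the per-protocol comparison of week-4 scores. If patients who did poorly are the ones who reach for drugs, the set loses poor responders, and loses more of them in arms where the treatment does less. The same applies to ultraweak photon emission and metabolomics, which are measured only at baseline and end of treatment, if they are analysed in this set.

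What is at stake is how the sensitivity analysis can be read. A gap between it and the intention-to-treat result could reflect adherence during treatment or selection on what happened afterwards, and the two could not be told apart. Compatible versus single acupoint is the stated aim, and its planned difference is only 4 points.

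**Working it through.** **1. The windows side by side.** Weeks 1–4 are treatment, with the NDLQI at the end of week 4. Weeks 5–8 are follow-up, with the NDLQI again at the end. The drug criterion covers the whole trial, hence weeks 5–8. For a week-4 outcome those weeks come after measurement; for an end-of-follow-up outcome they come before it. One trial-wide window cannot suit both.

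**2. Starting figures (Sample size section).** Expected changes are 12, 8 and 4 (compatible, single, sham), with SDs 10, 13 and 13. The planned differences are 12 − 4 = 8, 12 − 8 = 4 and 8 − 4 = 4. The plan states no drug-use rate and no per-protocol figure, so there is nothing further to reproduce. Every rate below is an assumption.

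**3. One case by hand.** Let the change y be normal with mean μ and SD σ. Suppose follow-up drug use has probability a = 0.30 if y ≤ 0 and b = 0.05 otherwise, in all arms. Then:

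- q = Φ(−μ/σ), the share with no improvement
- e = μq − σφ(μ/σ), their contribution to the mean
- removed = aq + b(1 − q)
- retained mean = [(1 − b)(μ − e) + (1 − a)e] / (1 − removed)

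| Arm | q | e | removed | retained mean |
|---|---|---|---|---|
| Compatible | 0.115 | −0.561 | 0.079 | (0.95×12.561 − 0.70×0.561)/0.921 = 12.53 |
| Single | 0.269 | −2.138 | 0.117 | (0.95×10.138 − 0.70×2.138)/0.883 = 9.22 |
| Sham | 0.379 | −3.430 | 0.145 | (0.95×7.430 − 0.70×3.430)/0.855 = 5.45 |

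Compatible − sham = 7.08 (planned 8); compatible − single = 3.31 (planned 4).

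**4. Range of assumptions.** The logistic rows use P(drug) = 1/(1 + exp(−[base − ln(OR)·y/10])), so OR is the rise in odds per 10 points less improvement. They were evaluated by numerical integration. Arms are in the order compatible / single / sham.

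| Assumed pattern | Removed, % | Retained means | Comp − sham | Comp − single |
|---|---|---|---|---|
| 10% if y ≤ 0, else 2% | 2.9 / 4.2 / 5.0 | 12.2 / 8.4 / 4.4 | 7.7 | 3.8 |
| 20% if y ≤ 0, else 2% | 4.1 / 6.8 / 8.8 | 12.4 / 8.8 / 5.0 | 7.4 | 3.5 |
| 50% if y ≤ 0, else 5% | 10.2 / 17.1 / 22.1 | 13.0 / 10.3 / 6.9 | 6.1 | 2.6 |
| Logistic, base −2.5, OR 1.5 | 5.1 / 6.3 / 7.3 | 12.2 / 8.4 / 4.5 | 7.7 | 3.8 |
| Logistic, base −2.5, OR 3 | 3.6 / 6.9 / 9.6 | 12.4 / 9.1 / 5.5 | 6.9 | 3.3 |
| Logistic, base −1.0, OR 1.5 | 19.2 / 22.3 / 25.0 | 12.8 / 9.5 / 5.6 | 7.1 | 3.3 |
| Logistic, base −0.5, OR 3 | 18.4 / 26.7 / 33.6 | 13.7 / 11.7 / 8.6 | 5.1 | 2.0 |
| Unrelated to response, 5/10/20% | 5.0 / 10.0 / 20.0 | 12.0 / 8.0 / 4.0 | 8.0 | 4.0 |
| Relapse: 20% if y ≥ 12, else 5% | 12.5 / 10.7 / 9.0 | 11.3 / 7.2 / 3.3 | 8.0 | 4.15 |
| 30%/5% rule in the two active arms, flat 10% in sham | 7.9 / 11.7 / 10.0 | 12.5 / 9.2 / 4.0 | 8.5 | 3.3 |

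In the last row single − sham also widens, from 4 to about 5.2. At a still lower rate (base −3, OR 1.5; 3.2 to 4.6% removed) the two contrasts are 7.8 and 3.9.

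**5. With the window closed at the assessment.** Follow-up drug use removes nobody from the week-4 set, and this source of shift disappears under every pattern.

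**The case against.** **It is only an example, and the detail may sit in a plan not shown.** True in part: the words illustrate a major violation, and a full analysis plan may define windows. But the article itself sets the window as the whole trial, and nothing else in it narrows that. This is a stated rule that fits badly, not a missing one.

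**The primary result.** A reader might infer that the week-4 primary result is itself filtered. It is not: efficacy analyses include all randomized patients, and the per-protocol set serves only a sensitivity analysis.

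**Direction.** A reader might infer that the differences must shrink. The documents give no rates and no link between drug use and response. Shrinkage follows if poor responders take drugs under a similar rule in every arm, which is plausible but assumed. Other patterns give no shift or a wider contrast. The largest falls, to 5.1 and 2.0, need 18 to 34% of each arm to be excluded.

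**Scope of the drug rule.** A reader might also infer that the exclusion reaches drugs the protocol permits, since the Intervention section bars only treatments that may affect dyspepsia symptoms. The text does not support that. The example sits under protocol violations, and a permitted drug is not a violation. Cross-referring to the prohibition is a convenience, not the cure of a proven conflict.

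**Time point.** Under the Primary outcome section, follow-up drug use precedes or accompanies the endpoint, and excluding for it would be ordinary practice. That stands for end-of-follow-up outcomes. It does not rescue the rule for the week-4 comparison named in the Abstract, Sample size and Statistical analysis sections, nor for measures that stop at end of treatment.

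**Conclusion.** The point holds in limited form. As worded, the per-protocol sensitivity analysis of week-4 outcomes is conditioned on drug use after those outcomes were measured. If such use is commoner after poor response in all arms, the tabulated cases bring compatible-minus-sham down from 8 to about 7.7–5.1 and compatible-minus-single from 4 to about 3.8–2.0, and raise the sham mean change from 4 to about 4.4–8.6. These figures rest on the planning means and SDs, normal changes and assumed drug-use rates; they show sensitivity and do not predict. Without a link to response there is no shift, and if the link differs between arms a contrast can widen. Severity is low: the intention-to-treat primary analysis is untouched, and the harm is a supporting analysis that would be hard to interpret.

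**What to change.** Define per-protocol membership separately for each assessment. In place of the trial-wide drug example, state that a patient is excluded for taking a treatment prohibited in the Intervention section before the assessment being analysed: up to week 4 for week-4 and other end-of-treatment outcomes, up to week 8 for end-of-follow-up outcomes. The 16-session criterion can stay as it is.

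Separately, reconcile the Primary outcome section with the Abstract, Sample size and Statistical analysis sections on the primary time point. The per-assessment rule works whichever is confirmed.

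The cost is one sentence in the analysis section, plus dates of drug use in the case report form so that each violation can be placed before or after an assessment. No extra patients or visits are needed. The change should be made before unblinding.
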